## Abstract

**Background:**

Persistent neck pain is a prevalent musculoskeletal condition that affects the quality of life and functional abilities of individuals. Blood Flow Restriction Training (BFRT) is a novel therapeutic approach that involves restricting blood flow to exercising muscles to enhance strength and function. However, limited research has been conducted on the effects of BFRT on pressure pain threshold and hand function in adults with persistent neck pain. This randomized controlled trial aims to investigate the potential benefits of BFRT as a treatment intervention for this population.

**Methods:**

This study will be a prospective 1:1 allocation, parallel group active controlled trail conducted at Physiotherapy Department, Galgotias University. The trial was prospectively registered with the Clinical Trial Registry India CTRI/2023/06/053439. Informed consent will be obtained from all the participants who are eligible to be included in the study. A total of 110 patients with persistent neck pain will be randomly allocated into two groups. The BFRT group will receive supervised training sessions three times a week for eight weeks, performing low-load resistance exercises with blood flow restriction applied using personalized cuff pressure. The control group will receive standard care for neck pain, which may include general advice, manual therapy, and/or home exercises without BFRT. The primary outcome measures will be the pressure pain threshold, assessed using a pressure Algometer, and hand function, evaluated using standardized tests such as Hand Grip Strength and Purdue Peg board Test.

**Results:**

The data obtained will be analyzed using appropriate statistical methods, and the significance level will be set at p<0.05.

**Conclusion:**

This trial will contribute valuable contribution highlighting the potential benefits of BFR training in improving pressure pain threshold and hand function in adults with persistent neck pain.

## Introduction

Persistent neck pain is a prevalent and debilitating condition that affects a significant number of adults worldwide.
^
1
^ The burden of this condition on individuals’ quality of life and productivity underscores the need for effective and innovative interventions to alleviate pain and improve functional outcomes.
^
2
^ Exercise serves as the principal non-pharmacological approach to ameliorate function in musculoskeletal disorders that cause pain. Resistance training regimen for the muscles has been shown to increase pain threshold and improve function, thereby alleviating discomfort. In order to induce muscle strength gain, the American College of Sports Medicine (ACSM) advises a resistance load of 60% to 70% of one repetition maximum (RM). At the same time, studies have reported that resistance training with increased loads leads to heightened stress levels, consequently resulting in increased pain, reduced patient adherence, and potential condition deterioration. Therefore, researchers have turned their attention towards developing a suitable resistance training program that is less taxing and more tolerable for individuals suffering with painful neck conditions. BFRT is one method that permits a pairing with low intensity resistance load while still offering the potential to generate an equivalent increase in muscular strength as the advised resistance training regimens with relatively high loads. Beneficial physiological effects of BFRT include recruitment of type II muscle fibers and stimulation of growth hormone activity induced by partial vascular occlusion, in addition to its mechanical advantages. BFRT procedure paired with low intensity resisted exercise are proposed to cause pain modulation by exercise induced hypoalgesia (EIH) and conditioned pain modulation (CPM) pathways by activating descending pain inhibition.

Blood flow restriction (BFR) training has emerged as a promising technique that has shown potential benefits in enhancing muscular strength and promoting tissue adaptation without subjecting the body to high-intensity exercises.
^
3
^ Despite its applications in various musculoskeletal conditions, the potential efficacy of BFR training in managing persistent neck pain remains relatively unexplored. This study protocol aims to investigate the effect of blood flow restriction training on pressure pain threshold and hand function among adults suffering from persistent neck pain. Utilizing a randomized controlled trial design, this research seeks to provide valuable insights into the role of BFR training as a potential therapeutic option for this challenging and often refractory condition. The rationale for examining pressure pain threshold lies in its significance as a common clinical measure for assessing pain sensitivity and tolerance, particularly in musculoskeletal pain conditions.
^
4
^ Understanding the impact of BFR training on pressure pain threshold will offer valuable information on the technique’s ability to modulate pain perception in individuals with persistent neck pain. Additionally, assessing hand function is of paramount importance, as neck pain can often result in functional limitations that affect daily activities and work performance.
^
5
^ Investigating the effects of BFR training on hand function will shed light on whether this intervention can lead to functional improvements and enhance the overall well-being of individuals experiencing neck pain. The results obtained from this research hold the potential to inform healthcare practitioners, physiotherapists, and other relevant professionals about the feasibility and effectiveness of incorporating BFR training into the management strategies for individuals with persistent neck pain. By addressing the current research gap and exploring the impact of BFR training on pressure pain threshold and hand function, this study protocol aspires to contribute to evidence-based practices in pain management and rehabilitation, ultimately enhancing the quality of life for those affected by persistent neck pain.

## Objectives

I.To evaluate the effect of BFRT in alleviating neck pain and improving the hand function among adults with persistent neck pain.II.To study the impact of BFRT on activities of daily living and quality of life among patients with persistent neck pain.III.To study the long term effect of BFRT on precision and power grip among adults with persistent neck pain.

## Protocol

### Study design

This study will be a prospective 1:1 allocation, parallel group active controlled trail conducted at Physiotherapy Department, Galgotias University
*.* Ethical clearance has been obtained from Departmental Ethics Committee on 19/05/2023 with reference number DEC/PT/GU/2023 and the trial was prospectively registered with the Clinical Trial Registry India CTRI/2023/06/053439. Informed consent will be obtained from all the participants who are eligible to be included in the study.

### Null hypothesis

There is no difference between the BFRT and conventional physiotherapy group in alleviation of pain, and hand function among adults with neck pain.

### Alternate hypothesis

BFRT will have a significant impact in reducing pressure pain threshold and improving hand function in patients with persistent neck pain among adults.

**
*Subjects*
**

One hundred and ten self-reporting persistent neck pain for more than three months duration will be screened for eligibility and recruited in the study. After obtaining informed consent, the participants will be randomly allocated in 1:1 ratio to the BFR training group and the control group using a computer-generated randomization sequence. Allocation concealment will be ensured to maintain blinding and reduce potential bias. Sample size was calculated using Gpower version 3.1.9.4 for Windows by assuming effect size of 0.5(Cohen’s D medium size effect was assumed) with the margin of error (α) to test the level of significance was set at 0.05 and (1-α) 80% βpower and confidence interval at 95%, the final derived sample with added 10% of contingency was n=112
^
6
^ (
Figure 1). See
Figure 2 for central and non-central distributions.

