## Discussion

The present study protocol presents a RCT testing the effectiveness of BFRT on pressure pain threshold and hand function among adults with persistent neck pain. The intervention aims to reduce pain and hand function by the proposed mechanism. The study intends to employ a randomized controlled trial design, ensuring scientific rigor and minimizing bias. By comparing the BFR training intervention group with a control group, researchers seek to assess the impact of this innovative technique on two primary outcomes: pressure pain threshold and hand function. Therefore, we expect that the adults with neck pain and compromised hand function in the BFRT group will exhibit improvement in terms of pain and hand function in comparison to the neck pain patients in the conventional group. The significance of this research lies in its potential to contribute valuable insights into managing neck pain and improving hand function using a novel approach like BFR training. If the results show positive effects, it could pave the way for a non-invasive, safe, and cost-effective intervention for individuals dealing with persistent neck pain. Ultimately, this study may have a meaningful impact on the quality of life for those suffering from this prevalent issue, offering hope for improved pain management and functional recovery.

**Study Status**: At the moment the authors are involved in training the assessors and physiotherapists those who will be involved in interventions and we are planning to start screening after one month.

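### The alternative hypothesis gives the wrong direction for a primary outcome: it predicts a fall in pressure pain threshold, whereas the rationale treats a rise as the benefit

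*Protocol article*

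**What the plan says.** The Abstract (Methods) and the Discussion name PPT and hand function as the primary outcomes. Under Alternate hypothesis the article predicts: "BFRT will have a significant impact in reducing pressure pain threshold and improving hand function". The null hypothesis has no direction: "There is no difference between the BFRT and conventional physiotherapy group in alleviation of pain, and hand function".

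The Outcome measures section describes PPT as pressure in kPa, applied with an algometer and raised until the participant reports pain. The Introduction says of exercise in general: "Resistance training regimen for the muscles has been shown to increase pain threshold and improve function, thereby alleviating discomfort". It proposes that BFRT with low-load exercise will "cause pain modulation by exercise induced hypoalgesia (EIH) and conditioned pain modulation (CPM) pathways". The abstract's Conclusion refers to the "potential benefits of BFR training in improving pressure pain threshold and hand function". The Discussion expects the BFRT group to improve in both pain and hand function compared with control, but also says: "The intervention aims to reduce pain and hand function by the proposed mechanism".

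The sample size text (Subjects, under Alternate hypothesis) gives d = 0.5, α = 0.05, 80% power and a 10% contingency, leading to n=112; 110 participants are to be randomised. Neither that text nor the Statistical analysis section says whether the test has one or two sides.

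**The concern.** The hypothesis is the pre-specified statement against which the result will be judged, and for one of two primary outcomes it points the opposite way from the rationale. If BFRT works as the Introduction proposes, PPT rises and the formal alternative is contradicted. If BFRT makes the neck more pressure-sensitive, the formal alternative is met.

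If the error is found only once results are known, the authors will have to reverse the stated direction after seeing data, and a reader cannot then tell a slip of wording from a change of hypothesis. Neither the hypothesis nor the outcome section says which direction of PPT is beneficial, so nothing next to the error corrects it.

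The wording would also matter for the test if the test is directional, which is why sidedness has to be checked.

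**Working it through.** **Step 1: direction.** The statements bearing on PPT or pain, side by side:

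| Place | What it implies |
|---|---|
| Outcome measures | PPT is the pressure at which pain is reported; a lower value means pain at less pressure |
| Introduction, exercise | a higher threshold is the benefit |
| Introduction, mechanism | hypoalgesia, hence a higher PPT |
| Abstract, Conclusion | PPT improves |
| Null hypothesis | the question is relief of pain |
| Discussion, expectation | pain improves on BFRT |
| Alternate hypothesis | PPT falls |

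Only the last row points the other way. The hand-function half of the same hypothesis is correctly directed. The Discussion sentence on the intervention's aim has a separate slip: read literally, it makes less hand function an aim.

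**Step 2: reproduce the sample size.** Inputs from the article: d = 0.5, α = 0.05, power 0.80, 1:1 allocation, 10% contingency. The normal approximation is n per arm = 2(z_α + z_β)²/d².

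- One-sided: 2 × (1.645 + 0.842)²/0.25 = 49.5, so 50 per arm, 100 in total; 100/0.9 = 111.1, so 112.
- One-sided, exact noncentral t: 51 per arm, 102 in total; 102 × 1.1 = 112.2, which matches 112.
- Two-sided, normal approximation: 2 × (1.960 + 0.842)²/0.25 = 62.8, so 63 per arm, 126 in total; 126 × 1.1 = 138.6, or 126/0.9 = 140.
- Two-sided, exact noncentral t: 64 per arm, 128 in total; 128 × 1.1 = 140.8, or 128/0.9 = 142.2, so 143.

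The stated 112 is reached only with one tail. The calculation uses d without a sign, so correcting the direction of the hypothesis leaves n unchanged.

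**Step 3: power at the planned size for a true d of 0.5 in the beneficial direction** (noncentral t). With 55 per arm, df = 108 and the noncentrality parameter is 0.5 × √(55/2) = 2.62.

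| Total randomised | One-sided, beneficial direction | Two-sided |
|---|---|---|
| 110 | 0.83 | 0.74 |
| 112 | 0.84 | 0.75 |

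These figures assume that everyone randomised is analysed. With 102 analysed (the one-sided requirement before contingency), they are 0.81 and 0.71.

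**The case against.** A reader might infer that the primary test looks in the wrong tail. A one-sided 5% test for a fall in PPT, with 55 per arm and a true benefit of d = 0.5, would have power P(T < −1.659) of about 0.00001, against 0.83 in the beneficial direction. The arithmetic is right, but the article does not support the premise. It nowhere plans a one-sided analysis: the null is one of no difference, and the article gives only a 5% significance level and a Student's t-test. If that test is two-sided, the wording of the alternative leaves the rejection region where it is and a rise in PPT would be detected. The 0.00001 is therefore a hypothetical, not a property of the plan.

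The one-tailed inference also concerns the sample size calculation, which names no outcome and would fit the correctly directed hand-function half equally well. The two sample size figures are not shown and might settle which tails were used.

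Finally, the intent is plain from the rest of the article, and the authors very probably meant less pain or a higher threshold. The Discussion slip is clarified a few sentences later by the stated expectation of improvement.

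All of this stands, and it limits the damage. It does not make the hypothesis sentence right, nor does it supply the missing statement of sidedness.

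**Conclusion.** The point holds as an error of direction in the formal hypothesis for a primary outcome. It rests on the article's own description of PPT and its own rationale; no outside source is needed.

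The statistical effect depends on sidedness. With a two-sided test, the wrong direction changes neither the p-value nor the power. The test itself is harmed only if it is run one-sided in the written direction, which the article does not state. Sidedness still needs to be settled, because n=112 reproduces only as a one-tailed calculation. If the analysis is two-sided, power at the article's own d of 0.5 is about 74% with 110 participants or 75% with 112, against the stated 80%, before any loss to follow-up.

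**What to change.** 1. Restate the alternative: BFRT increases PPT and improves hand function relative to control.
2. Define benefit beside the hypothesis: a higher PPT and better scores on the hand-function measures.
3. Correct the Discussion sentence so that the aim is to reduce pain and to improve hand function.
4. State separately whether the sample size calculation and the analysis are one-sided or two-sided.

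Items 1 to 3 cost a few sentences and leave n unchanged. The Discussion's study status note says that screening had not begun when the article was written; a correction made before any data are seen raises no suspicion of a changed hypothesis.

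Item 4 has a cost if the answer is two-sided. The sponsor would then either restate power at d = 0.5 as about 74% with 110 participants (75% with 112), or keep 80% and plan for 126 to 128 evaluable participants, about 139 to 143 with the 10% contingency. Correcting the direction does not require that choice, nor does it require naming a primary time point. Table 1 schedules PPT and hand function both after the intervention and at follow-up, and this correction need not choose between them.

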### Outcome measures

**
*Pressure pain threshold using Algometer*
**

Using an algometer, a portable instrument that measures pressure sensitivity at particular anatomical locations in the neck region, the pressure pain threshold (PPT) will be determined. The algometer consists of a gauge with a pressure-sensing tip attached that measures applied pressure in kilopascals (kPa). Before the assessments begins, the algometer will be calibrated to ensure accuracy and consistency of measurements. Participants will be comfortably seated in an upright position with their neck muscles relaxed. It is essential to explain the procedure to the participant, ensuring they understand the assessment and can provide feedback on their pain perception. Specific anatomical points in the neck region will be chosen for the assessment. Commonly, these points include the trapezius, levator scapulae, and sternocleidomastoid muscles. The researcher will progressively apply pressure to the selected spots using the algometer. A button must be pressed to cease the pressure application or the participant must verbally report feeling pain for the pressure to increase at a constant rate (for example, 1 kPa/s).

**
*Neck Outcome Score*
**

The Neck Outcome Score (NOS) is a self-reported questionnaire that assesses various aspects of neck pain and its impact on daily activities and quality of life. Participants will be provided with the NOS questionnaire, and the research team will explain its purpose and how to complete it. It’s important to ensure that participants understand the questions and how to score their responses accurately. The NOS typically includes questions related to pain intensity, pain-related disability, functional limitations, and the impact of neck pain on quality of life.

**
*Grip strength using hand help dynamometer*
**

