Grip strength will be measured using a handheld dynamometer. We will ensure that the participant is well-rested and not fatigued before the measurement. We will also inform the participant about the purpose of the grip strength measurement and the procedure involved. The dynamometer will be adjusted to fit the participant’s hand size. The participant will be seated on a chair without armrests, ensuring proper posture with their back straight, feet flat on the ground, and forearm resting on a flat surface. We will instruct the participant to hold the dynamometer in their dominant hand. When the participant is ready, they should be instructed to squeeze the dynamometer handle with maximum effort for about 3 to 5 seconds. The researcher can provide encouragement to the participant during the measurement to ensure they exert their maximum effort. The highest grip strength measurement achieved during the trial will be recorded.

**
*WHO-5 quality of life index questionnaire*
**

The WHO-5 quality of life index questionnaire is used to assess an individual’s subjective well-being and quality of life. We will briefly explain the purpose of the WHO-5 questionnaire to the participant and let them know that it’s designed to assess their emotional well-being and quality of life. Participants will rate their agreement with each statement on a scale from 0 to 5, where 0 indicates “at no time” and 5 indicates “all of the time”. After participants have provided their responses, we can assist them in calculating their total score. A higher score on the WHO-5 indicates better emotional well-being and quality of life.

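### Allocation concealment is credited with maintaining blinding, which it cannot do after assignment, so pressure pain threshold and grip strength have no stated protection against differential assessment

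*Protocol article*

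**What the plan says.** The Subjects paragraph, under Alternate hypothesis, describes a computer-generated 1:1 sequence and then says: "Allocation concealment will be ensured to maintain blinding and reduce potential bias". Blinding is mentioned nowhere else in the article.

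The Abstract and the Discussion both name the primary outcomes: "two primary outcomes: pressure pain threshold and hand function". The Abstract defines hand function by grip strength and the Purdue pegboard.

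Under Outcome measures:
- **PPT:** "The researcher will progressively apply pressure to the selected spots using the algometer". The sentence on rate and endpoint is garbled: "the participant must verbally report feeling pain for the pressure to increase at a constant rate (for example, 1 kPa/s". The algometer is to be calibrated beforehand.
- **Grip strength:** "The researcher can provide encouragement to the participant during the measurement to ensure they exert their maximum effort", and "The highest grip strength measurement achieved during the trial will be recorded".
- **Purdue pegboard:** no description of how it is administered.

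On the arms, the Abstract gives the experimental group supervised cuff training three times a week for eight weeks and the control group standard care without it. The Intervention section says all patients will have the procedure and its possible benefits explained to them. It describes no sham cuff. The study status note in the Discussion says the team is "training the assessors and physiotherapists those who will be involved in interventions" and that screening has not begun.

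**The concern.** Allocation concealment and blinding are different safeguards. Concealment prevents selection bias: whoever recruits cannot foresee the next assignment. Its work ends at assignment. Blinding acts after that point and prevents treatment and measurement from differing by arm. The article offers the first as the means to the second and relies on it to reduce bias. This is an error in a stated safeguard, which is a different matter from detail left to a fuller document.

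It matters here because of the outcomes. PPT depends on how a person applies pressure and when another person reports pain. Grip is a maximum-effort test in which coaching can change the reading, and coaching is left to discretion. If the tester knows the arm, either reading can shift in one arm and not the other. The planned t-tests and regression cannot tell such a shift from a treatment effect.

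**Working it through.** **Step 1. Who could be blind under the text as written?**

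| Group | What the article gives | Consequence |
|---|---|---|
| Recruiter, before assignment | Computer-generated sequence, concealment | Protected |
| Participants | Cuff training or no cuff; no sham; procedure explained to all | Cannot be blind |
| Therapists | Deliver the cuff sessions | Cannot be blind |
| Assessors | Named as a role being trained; nothing on masking | Could be blind; not stated |

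Concealment covers the first row only. The fourth row is the one group that could be blinded after assignment, and the text is silent on it.

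**Step 2. Where can the assessor influence the reading?**

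- PPT: through the hand-applied ramp. The text asks for a constant rate but gives the figure only as an example. The apparent intention is that a button press or the participant's report ends the test, so the participant's own expectation also enters.
- Grip: through encouragement, which is permitted and not scripted. The highest value is kept.
- Pegboard: cannot be judged, because no procedure is given.

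**Step 3. The plan's own figure.** This point challenges no number. The one design figure in the same paragraph is the total of 112 (effect size 0.5, significance level 0.05, power 80%, 10% contingency). A one-sided t-test needs 51 per arm, and 102 × 1.10 = 112.2, which agrees. A two-sided test needs 64 per arm, and 128 × 1.10 = 140.8, which does not. The article does not state the sidedness, so both are shown below.

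**Step 4. What a shift would do.** The documents give no bias figure, so the shift *b* (in SD units) is an assumption.

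Expected observed difference = true effect + *b*.

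With no true effect and *n* per arm, the t statistic is noncentral t with 2*n* − 2 degrees of freedom and noncentrality *b*√(*n*/2). The article recruits 110, so *n* = 110/2 = 55, degrees of freedom = 108 and √(55/2) = 5.244.

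| Assumed *b* (SD) | Noncentrality | Rejections, two-sided 5% | Rejections, one-sided 5% |
|---|---|---|---|
| 0 | 0 | 5.0% | 5.0% |
| 0.1 | 0.524 | 8.1% | 13.1% |
| 0.2 | 1.049 | 18.0% | 27.3% |
| 0.3 | 1.573 | 34.5% | 46.8% |

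With 56 per arm (total 112), the two-sided figures are 8.2%, 18.2% and 35.0%, so the choice between 110 and 112 is immaterial. A shift of 0.2 SD is 0.2/0.5 = 40% of the effect the trial was sized to detect. The table assumes a shift in favour of the experimental arm. A shift the other way would hide a real benefit.

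**The case against.** The strongest reply is that the harm rests on silence. Assessment is biased only if testers know the arm, and the article never says they do. A condensed article commonly leaves the details of masking to the full protocol, and the study status note mentions assessors as well as physiotherapists. This stands in part. A reader might infer that outcomes will be measured by unblinded or treating staff, but the documents do not show that. Masking of assessors is unstated, not shown to be absent, and the note's wording does not settle whether the two roles are separate. The reply does not rescue the sentence on concealment, which is wrong whatever a fuller document contains.

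Second, PPT already has some protection: calibration, a constant ramp and an endpoint that appears to rest with the participant. This stands too, and it narrows the assessor's room. It also means that much of the remaining risk in PPT comes from participants who know their arm, which masked assessors would not remove.

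Third, the grip instruction is the same for everyone. That is correct: the text permits uneven encouragement but does not prescribe it, and it would be wrong to read it as a plan to coach the arms differently.

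Fourth, the error rates are simply the power curve at 55 per arm and would apply to any trial of that size. Agreed. They show how sensitive the test is to a shift and say nothing about whether one will occur here.

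**Conclusion.** The point holds in limited form. The article credits allocation concealment with an effect it cannot have. Participants and therapists cannot be blind in this design as described, and nothing stated protects PPT or grip from differential assessment. That is a gap in stated protection, not evidence of actual bias. It is not shown for every component of the primary outcomes: the pegboard cannot be judged, and the encouragement issue applies to grip alone.

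The size is unknown. The range of about 8% to 35% in place of 5% rests wholly on an assumed shift of 0.1 to 0.3 SD, 55 per arm, no true effect and a two-sided test. Correction is worthwhile because the stated safeguard is wrong, the outcomes depend on effort or report, and the remedy is cheap before screening starts and unavailable once data have been collected.

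**What to change.** Replace the single sentence with two separate statements, and amend the grip instruction:

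1. **Concealment.** The sequence is held by someone outside recruitment and is not accessible to recruiters until the participant is assigned.
2. **Blinding.** PPT and hand-function tests at T0, T1 and T2 are done by the assessors now being trained, who deliver no trial treatment and have no access to allocation. Participants are asked not to disclose their arm to them. Participants and therapists are unblinded. Masking the assessors does not remove participant expectation from PPT, and that limitation is to be acknowledged.
3. **Grip.** Make encouragement one fixed script, used identically for every participant and visit.

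While that section is open, the garbled PPT sentence should be repaired and one rate fixed for all tests.

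The cost is protocol wording, a short script and a rota rule, with no change to the sample size. The downside is that scheduling must keep assessors and treating physiotherapists apart. This assumes the assessors in training can be kept out of treatment. If they are the same people as the therapists, someone else will be needed for testing and the cost rises accordingly.

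### The sample size of 112 comes only from a one-tailed calculation, so the two-sided comparison has about 69–75% power rather than 80%; the target is also given as both 110 and 112

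*Protocol article*

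**What the plan says.** The sample-size statement is in the Subjects paragraph under Alternate hypothesis in the protocol article. The calculation was done in G*Power, "assuming effect size of 0.5(Cohen’s D medium size effect was assumed". Alpha is 0.05. The phrase on power is garbled; I read it as 80% power and a 95% confidence interval. The outcome of the calculation is reported thus: "the final derived sample with added 10% of contingency was n=112". The number of tails is not stated.

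The same paragraph opens with a different number: "One hundred and ten self-reporting persistent neck pain for more than three months duration will be screened for eligibility and recruited". The Abstract (Methods) agrees with that one: "A total of 110 patients with persistent neck pain will be randomly allocated into two groups".

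Three other places bear on sidedness:
- Null hypothesis: "There is no difference between the BFRT and conventional physiotherapy group in alleviation of pain".
- Abstract (Results): "the significance level will be set at p<0.05".
- Statistical analysis: a Student's t-test between the groups, with no direction specified.

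**The concern.** Every input to the calculation is published except the number of tails, and 112 looks too small. A two-sample t-test for d = 0.5 at two-sided 0.05 with 80% power is known to need 64 per arm, so 128 patients before any allowance for loss. A total of 112 that already includes 10% cannot come from that test.

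If the groups are compared two-sided, which is how the rest of the article reads, the 80% is not a property of the design. The trial would miss the effect it was sized for more often than stated, and a non-significant result would be read as stronger evidence against benefit than it is. The two enrolment targets add a smaller doubt about which number the trial is committed to.

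**Working it through.** **Inputs.** Sample-size paragraph: d = 0.5, alpha = 0.05, power 80%, 1:1 allocation, 10% added. Statistical analysis: independent-samples t-test.

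**Formula.** With n per arm, the t statistic has 2n − 2 degrees of freedom and noncentrality d × √(n/2). Power is the probability that it exceeds the critical value: the 95th percentile of central t for one tail, or ±the 97.5th percentile for two tails.

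**Step 1: reproduce 112.**

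| Test | n per arm for 80% | Rounded | Total | × 1.10 | ÷ 0.90 |
|---|---|---|---|---|---|
| One-tailed | 50.15 | 51 | 102 | 112.2 | 113.3 |
| Two-tailed | 63.77 | 64 | 128 | 140.8 | 142.2 |

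The one-tailed row with × 1.10 gives the stated 112.

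**Step 2: try other routes to 112.**
- Two-sided normal approximation: 126 before contingency, and 139 or 140 after.
- One-sided normal approximation: 100, and 100/0.9 = 111.1, which rounds up to 112. This also matches, but it is one-sided too.
- Paired or one-sample t-test: 27 (one-sided) or 34 (two-sided), far too few.
- Two-sided rank test: 134 to 148 before contingency.

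No two-sided between-group calculation gives 112. Even before contingency, each needs more than that.

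**Step 3: power at the planned numbers, d = 0.5.**

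| Analysed | Where the number comes from | Two-sided power | One-sided power | Two-sided detectable d at 80% |
|---|---|---|---|---|
| 112 | derived N, no loss | 74.6% | 83.8% | 0.53 |
| 110 | stated enrolment, no loss | 73.8% | 83.2% | 0.54 |
| 102 | N before contingency | 70.6% | 80.6% | 0.56 |
| 99 | 110 × 0.90 | 69.2% | 79.5% | 0.57 |
| 128 | two-sided requirement | 80.2% | 87.9% | 0.50 |

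For example, with 110 analysed the noncentrality is 0.5 × √(55/2) = 2.622 on 108 degrees of freedom. The two-sided critical value is 1.982 and the power 73.8%. The chance of missing d = 0.5 is one minus power: 25.4% at 112, 26.2% at 110 and 30.8% at 99.

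**Step 4: what baseline adjustment would recover.** Pressure pain threshold and hand function are measured at baseline and post-intervention (Table 1). Adjusting for baseline with correlation r raises the effective standardised difference to 0.5/√(1 − r²). The article gives no r, so these values are assumptions:

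| Assumed r | Effective d | n per arm | Evaluable total for 80%, two-sided |
|---|---|---|---|
| 0.3 | 0.524 | 58.12 | 118 |
| 0.4 | 0.546 | 53.72 | 108 |
| 0.5 | 0.577 | 48.07 | 98 |
| 0.6 | 0.625 | 41.17 | 84 |

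With 99 evaluable, 80% power is reached if r is about 0.5 or more, but not if it is 0.4 or less.

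**The case against.** The arithmetic is not in dispute; the inference that the test is two-sided is. The article never uses that word. The alternate hypothesis is directional, and the Discussion expects the BFRT group to do better. A null of no difference is often paired with a one-sided alternative, and on that reading 112 is adequate: one-sided power is 80.6% with 102 evaluable. Figures 1 and 2, which illustrate this calculation, are not available here and may show the number of tails.

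Part of this stands. Sidedness is inferred, not stated. But an expected direction does not declare a one-sided test, and the same sentence that gives alpha 0.05 pairs it with a 95% confidence interval, which is the two-sided convention. The direction written for pain threshold is also unusable: the alternate hypothesis has BFRT lowering the threshold, which means greater sensitivity, while the Discussion expects pain to improve. A one-sided test in that direction would look for harm. The figures could confirm a one-tailed setting, but they could not rescue a two-tailed one, because no two-tailed setting gives 112.

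Two smaller objections are fair. The gap between 110 and 112 moves power by less than one percentage point and would not matter alone. The lowest power figure, at 99, combines that gap with full 10% loss; at the plan's own evaluable number of 102, power is 70.6%.

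**Conclusion.** The concern holds. The stated 112 is a one-tailed figure, while the text describes a two-sided comparison. For d = 0.5 at two-sided 0.05, power is about 74% with 110 analysed and about 69% after 10% loss, against the stated 80%. The effect detectable with 80% power is d = 0.54 to 0.57, not 0.50.

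This rests on an unadjusted two-sample t-test, equal arms and the article's own d, alpha and contingency. It also rests on reading the comparison as two-sided, which the visible text supports but does not say. If one-sided testing was intended, the paragraph still needs correcting, because that choice is undeclared and the direction given for pain threshold is wrong. The 110 versus 112 discrepancy is a minor inconsistency that should be settled in the same edit.

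**What to change.** Revise the sample-size paragraph and the Abstract before screening starts; the study status note in the Discussion says it has not begun.

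1. State that the between-group test is two-sided at 0.05.
2. Use one target number throughout, in place of 110 and 112.
3. Restate what the design delivers. With 110 enrolled, that is about 74% power for d = 0.5 if all are analysed and about 69% after 10% loss; equivalently, 80% power for d = 0.54 to 0.57.
4. Correct the notation so that 80% is labelled 1 − β.

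This costs wording only and needs no extra patients. The stated power becomes less favourable.

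If the sponsor wants to keep an 80% claim, there are two sound routes:
- Keep 110 and make the primary comparison a baseline-adjusted analysis (ANCOVA). State the assumed baseline-to-post correlation and show a range; about 0.5 is needed with 99 evaluable. This replaces the unadjusted t-test in the Statistical analysis section.
- Enrol 141 (128 × 1.10), or 144 in equal arms if the 10% is taken as loss (128/0.9 = 142.2, so 143, rounded up to an even number). This adds 31 to 34 patients to the 110.

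Declaring a one-sided test would make 112 consistent. It would have to be justified, its direction for pain threshold corrected, and the analysis and confidence interval changed to match.
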